### Sample size calculation

Based on the findings of the preliminary survey, we estimated diarrhea prevalence in Idiofa Territory to be 10%. We also made an assumption that the intervention would reduce the prevalence by 2.5% (25% relative reduction) on the basis of systematic reviews. Unlike the previous studies, we calculated sample size on the basis of *Incidence density of diarrhea by ‘child-weeks’* using formula [28] as follows:

The expected value of s^2^ is given by:

E(s^2^) = *λ* Av(1/y_j_) + *σ*
^2^
_c_ = *λ*Av(1/y_j_) + k^2^
*λ*
^2^,where λ is the true mean rate, y_j_ is the child-weeks of follow up in the j^th^ cluster, Av(1/y_j_) indicates the mean over all m clusters, σ^2^
_c_ is the between-cluster variance of true rates, and k is the coefficient of variation of those rates (22). Using the preliminary survey, we were able to determine that the overall diarrheal rate for the 20 *quartiers* was 0.1 (or 10 per 100 child-weeks). The empirical standard deviation of the observed diarrhea rates was s = 0.051216, and the average of the reciprocal child-weeks per *quartier* was Av(1/y_j_) =0.022222, so that k was estimated as follows:$$ {\widehat{\sigma}}^2=0.0{51216}^2\hbox{--} \mathrm{0.10.022222}=0.000401,\mathrm{therefore},\mathrm{k}=\surd \left(0.000401/0.1\right)=0.063 $$

With an assumption that the diarrhea rate in control *quartiers* remains constant at λ_0_ = 0.1, we required 80% power (z_β_ = 1.96) if the intervention is to reduce the diarrhea rate by 25% to λ_1_ = 0.10×0.75=.075. Assuming y = 540 child-weeks of observation in each *quartier*, the number of *quartiers* required in each treatment group is given by:$$ \mathrm{c}=1+{\left(1.96+0.84\right)}^2\left[\left(0.1+0.075\right)/540+{0.063313}^2\left({0.1}^2+{0.075}^2\right)\right]/{\left(0.1-0.075\right)}^2=6.14 $$

Ignoring clustering, y = (1.96 + 0.84)^2^(0.1 + 0.075)/(0.1–0.075)^2^ = 2195.2 child-weeks per group, corresponding to 2195.2/540 = 4.07 *quartiers*. Thus, the expected design effect for this trial would be 6.14/4.07 = 1.51.

Assuming a coefficient of variation of 0.3 with 80% study power and 7.5% diarrheal prevalence in the intervention resulted in seven clusters (7 *quartiers*) per each arm. We increased the number of clusters to nine each in the control and intervention arm, and sampled 360 households in each trial arm. We will follow up at least 12 weeks to make 8640 child-weeks (‘child-weeks’ is the unit of the denominator) in each *quartier* as required to meet 80% power, considering a 12.5% loss to follow-up.

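### The between-quartier variance is net of Poisson noise although the survey input looks like a yes/no prevalence; if it is, k is about 0.25 rather than 0.20, and nine quartiers per arm miss 80% power on either reading

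*Protocol article*

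**What the plan says.** All of this is in the Protocol article, Methods/design, Sample size calculation.

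- The survey input is introduced as a proportion: "Based on the findings of the preliminary survey, we estimated diarrhea prevalence in Idiofa Territory to be 10" per cent. The same 0.1 is then used as a rate; the overall figure for 20 quartiers "was 0.1 (or 10 per 100 child-weeks").
- The expected empirical variance is written as λ·Av(1/y) + k²λ², where "σ^2^ _c_ is the between-cluster variance of true rates" and k is the coefficient of variation of those rates.
- The inputs are given as "The empirical standard deviation of the observed diarrhea rates was s = 0.051216" and "Av(1/y_j_) =0.022222, so that k was estimated as follows": 0.051216² less 0.1 × 0.022222 gives 0.000401, and k is printed as 0.063.
- With rates of 0.1 and 0.075 and 540 child-weeks per quartier, the plan states 6.14 quartiers per arm and a design effect of 1.51.
- The closing paragraph assumes a coefficient of variation of 0.3, with "80% study power and 7.5% diarrheal prevalence in the intervention" arm. It says this gives seven quartiers per arm and raises the number to nine.

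**The concern.** The subtracted term has to match how the survey datum arose. λ/y is the sampling variance of a rate of events that one child can repeat within the time observed. If each child gave one yes/no answer, the sampling variance of the observed proportion is λ(1−λ)/y, which is 10% smaller at λ = 0.1. The difference, 0.000222, is small beside s² but large beside what remains after subtraction, so it moves k noticeably.

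The point is distinct from the slip in turning the variance into k, because it lies in the 0.000401 itself. Someone who repaired only the conversion would get k = 0.20. At the most generous reading of follow-up that gives 79% power and appears to vindicate nine quartiers. Extra diary weeks do not reduce between-quartier variation, so an understated k means overstated power and a null result that could be read as stronger evidence than it is.

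**Working it through.** **Inputs** (all from Sample size calculation): s = 0.051216; Av(1/y) = 0.022222; λ₀ = 0.1; λ₁ = 0.075; y = 540; nine quartiers per arm; multipliers 1.96 and 0.84. The text prints z_β as 1.96, but the formula uses 0.84.

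**Plan's own figures.**
- s² = 0.051216² = 0.002623; less 0.1 × 0.022222 = 0.002222 leaves 0.000401. Reproduced.
- Printed k = √(0.000401/0.1) = 0.063. Reproduced as arithmetic, but the plan defines the variance as k²λ², so k should be √0.000401/0.1.
- Without clustering: 2195.2 child-weeks, or 4.07 quartiers. Reproduced.
- c = 1 + 7.84 × V/0.000625, with V = 0.175/y + k² × 0.015625. At k = 0.063313 and y = 540, V = 0.000387 and c = 5.85, not the printed 6.14; the design effect is 5.85/4.07 = 1.44, not 1.51.

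**Variance and k under the two noise terms.**
- Poisson: 0.002623 − 0.002222 = 0.000401; k = √0.000401/0.1 = 0.200.
- Binomial: 0.1 × 0.9 × 0.022222 = 0.002000; 0.002623 − 0.002000 = 0.000623; k = √0.000623/0.1 = 0.250. The exact moment form divides by 1 − 1/45 and gives 0.000637, k = 0.252.

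**Quartiers needed and power**, with power = Φ(√(8 × 0.000625/V) − 1.96), the plan's formula inverted at nine per arm, y = 540:

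| k | V | c | c/4.07 | Power |
|---|---|---|---|---|
| 0.063 (printed) | 0.000387 | 5.85 | 1.44 | 94.9% |
| 0.200 (conversion corrected) | 0.000950 | 12.9 | 3.2 | 63.1% |
| 0.250 (binomial noise as well) | 0.001298 | 17.3 | 4.2 | 50.1% |
| 0.3 (closing paragraph) | 0.001730 | 22.7 | 5.6 | 39.7% |

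The conversion slip therefore accounts for about 32 points and the noise term for about 13. A noncentral t with 16 df gives 62.7% and 49.9% for the middle two rows.

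**Other readings of follow-up.** 360/9 = 40 households per quartier; 40 × 12 weeks = 480; less 12.5% loss = 420. Forty children over a 52-week calendar give 2080. The text also says 8640 child-weeks in each quartier, although 720 × 12 = 8640 is the total for the whole trial.

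| y | Power, k = 0.20 | Power, k = 0.25 |
|---|---|---|
| 420 | 59% | 47% |
| 480 | 61% | 49% |
| 540 | 63% | 50% |
| 2080 | 76% | 58% |
| 8640 | 79% | 61% |

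**Precision of k.** With 20 quartiers (19 df, roughly normal quartier rates), the 95% interval for the variance behind s is 0.00152 to 0.00560. Its lower end is below either noise term, so k runs from 0 to √(0.00560 − 0.002222)/0.1 = 0.58 (Poisson) or √(0.00560 − 0.002000)/0.1 = 0.60 (binomial). Against binomial noise alone, chi-square is 24.9 on 19 df, p = 0.16.

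**Direction of the bias.** In 100,000 simulated surveys of 20 quartiers × 45 yes/no children with true variance 0.000625, the mean estimate was 0.000393 with the Poisson subtraction and about 0.00062 with the binomial one.

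**The case against.** **The yes/no premise is inferred.** The section says it works from incidence density, calls the inputs rates, and counts child-weeks; for repeatable events λ·Av(1/y) is the matching term. Av(1/y) is a mean of reciprocals and does not by itself show 45 children with one week each, and no survey question or recall period is given. This stands, so the point must be conditional. The yes/no reading is still the better supported: the figure is called a prevalence at the start and end of the section, 540 = 45 × 12, the trial measures prevalence by 7-day recall (Primary health outcome), and the Discussion puts episodes at 10–20 days, so two onsets in one child-week are hardly possible.

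**A reader might infer that this term takes power from 80% to 50%, or the design effect from 1.51 to 4.2.** The documents do not support that. Most of the loss comes from the conversion slip; the noise term adds about 13 points at y = 540.

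**A reader might also infer that over a third of the real between-quartier variance has been removed.** The point estimate is 36% lower (0.000222/0.000623), but the true variance is barely known, and 0.20 and 0.25 both lie well inside the interval for k. That is a reason to report a range. It is not a reason to keep a noise term that, for yes/no data, biases the estimate downward.

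**The closing paragraph's 0.3 exceeds 0.25.** So the last coefficient the plan states is not too small. But in the same formula it needs about 23 quartiers per arm at y = 540 (18.9 at y = 8640), not seven, so it does not rescue the power statement.

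**λ = 0.1 is itself doubtful.** Table 1 shows baseline under-four prevalence of 45.9% and 45.7%. With 0.458, a 25% reduction, k = 0.25 and y = 540, the formula gives about 59%. The restated power is thus power under the plan's own assumptions, not a forecast.

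**Conclusion.** The point holds in conditional form. If the preliminary survey gave one yes/no record per child, the subtracted noise is too large, the between-quartier variance estimate is 0.000623 rather than 0.000401, and k is about 0.25 rather than 0.20. At nine quartiers per arm and y = 540 this lowers power from 63% to about 50%, on top of the larger loss from the conversion slip. If the survey counted repeatable episodes, the Poisson term is right and power is 63%. With k computed by the plan's own definition, no reading of follow-up from 420 to 8640 child-weeks reaches 80%.

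This rests on the plan's formula, rates of 0.1 and 0.075, a two-sided 5% level implied by 1.96, and a k estimated very imprecisely from 20 quartiers.

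**What to change.** In Sample size calculation:

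1. Say what the preliminary survey recorded. If it was one yes/no answer per child, subtract λ(1−λ)·Av(1/y) in place of λ·Av(1/y). If it counted repeatable episodes, say so and keep λ·Av(1/y).
2. Compute k as √variance/λ: about 0.25, or 0.20 under the Poisson reading.
3. Restate power at nine quartiers per arm (about 50%, or 63%, at y = 540) and the design effect (about 4.2, or 3.2) as ranges, and note that k from 20 quartiers is very imprecise.
4. Reconcile this k with the coefficient of variation of 0.3 in the closing paragraph, which at y = 540 needs about 23 quartiers per arm and gives about 40% power at nine.

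The cost is recalculation and wording. No quartiers, households or follow-up are added, but the stated power becomes less favourable.

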In addition, the Sanitation Calendar is to be used as an effective method of tracking diarrhea for a registered child. With the Sanitation Calendar, the incidence density of diarrhea can be calculated by dividing diarrhea cases by observed child numbers multiplied by the specific duration observed (e.g. week, month, etc.). This would be a more effective tool since it would cause less fatigue among the respondents, who would otherwise be asked to provide information about their children’s diarrheal episodes on a daily basis by interviewers. Assuming that the incidence of diarrhea among children is three times a year on average [32], the number of days marked ‘O’ in mothers’ diaries will not be very high. As for the duration of diarrhea, it was estimated at 10–20 days on average. Except for the days marked with ‘O,’ all the other days will be considered ‘X’. The Sanitation Calendar allows the day-to-day observation of diarrhea and resolves the limitations associated with the small number of clusters in the trial. Previous studies were unable to identify the effect of improved sanitation on diarrheal duration because they relied on the period prevalence of reported diarrhea. The utilization of the Calendar will enable us to explore a relationship between sanitation improvements and diarrhea and investigate the extent to which well-equipped and appropriately managed latrines affect disease duration. The measurement relying on caregivers’ reports, which are subjective in nature, is one of the limitations of this study. As we will not be able to conduct laboratory tests to assess children’s diarrhea incidence, there may be under-reporting or over-reporting of diarrhea. Despite this risk, we do not expect any significant difference of reporting patterns between the people of the intervention and control *quartiers*.

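### The sample size enters a 10% survey prevalence as an incidence rate and treats repeated weeks on the same children as independent, so the 80% power tied to 12 weeks of diary is unsupported

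*Protocol article*

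**What the plan says.** All of this stands in the protocol article, mainly under Sample size calculation.

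- The planning figure starts as a prevalence: "we estimated diarrhea prevalence in Idiofa Territory to be 10"%. A few lines later the overall rate for the surveyed quartiers "was 0.1 (or 10 per 100 child-weeks").
- The calculation is labelled "Incidence density of diarrhea by ‘child-weeks". The Discussion defines incidence density as cases divided by child-time.
- The target is a 25% relative reduction, 0.1 to 0.075: "if the intervention is to reduce the diarrhea rate by 25"%. The next paragraph of the same section calls the 7.5% a prevalence.
- The amount of observation is fixed at "Assuming y = 540 child-weeks of observation in each" quartier. The variance has two terms, λ/y within quartiers and k²λ² between them.
- The sample is nine quartiers and 360 households per arm, with one registered child per household. On follow-up: "We will follow up at least 12 weeks to make 8640 child-weeks", with 12.5% loss.
- The Discussion, on the Sanitation Calendar, assumes three diarrhea episodes a year and adds: "As for the duration of diarrhea, it was estimated at 10–20 days on average".

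**The concern.** The term λ/y is right when events are independent over child-time. Here one child supplies at least 12 successive weeks. If a week is scored ill or not ill, an episode of 10–20 days marks several neighbouring weeks of the same child, and those weeks carry less information than the same number of weeks from different children.

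The preliminary survey's mean reciprocal of 0.022222 is 1/45. This fits about 45 children seen for one week each, where child-weeks and children are the same thing. Carrying a one-week proportion forward to 540 child-weeks changes its meaning: it is either a repeated status, which is correlated, or an onset rate, which should be lower.

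At stake is the stated power. If a trial described as 80% powered finds no difference, readers may take that as evidence that latrines have no effect.

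**Working it through.** **Formula.** The article's own: c = 1 + (1.96+0.84)²·V/(λ0−λ1)², with V = f(λ0+λ1)/y + k²(λ0²+λ1²). The factor f is added here; the article has f = 1. Power at nine per arm is Φ(√(8(λ0−λ1)²/V) − 1.96). The text reads "we required 80% power (z_β_ = 1.96"), but the formula uses 0.84 for power, as it should.

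**The plan's figure.** λ0 = 0.1, λ1 = 0.075, y = 540, k = 0.063313. V = 0.175/540 + 0.063313²×0.015625 = 0.000324 + 0.000063 = 0.000387. c = 1 + 7.84×0.000387/0.000625 = 5.85, not the printed 6.14 (y = 504 would give 6.14). Power at nine per arm is 95%.

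**k.** The article defines k as the coefficient of variation, so k = √0.000401/0.1 = 0.20; it prints √(0.000401/0.1) = 0.063. At k = 0.20, y = 540 and f = 1, c = 12.9 and power is 63%. Both values of k are carried below.

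**Child-weeks.** 360/9 = 40 children per quartier. 40×12 = 480 child-weeks, or 35×12 = 420 after 12.5% loss. 720×12 = 8640 is the total for the whole trial. 540 would be 45×12, which is an inference; the article does not say how it arises.

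**Reading A: a week is ill or not ill, at 10%.** Assumptions: random episode starts, fixed length D days, no other differences between children. A week is ill if an episode starts within a window of L = D + 6 days. Two weeks l apart share o = max(0, L − 7l) start days, which gives correlation ρ_l = 9(0.9^(−o/L) − 1). Over 12 weeks the variance is 1 + 2Σ(1 − l/12)ρ_l times binomial. Multiplying by 0.9 puts it relative to λ/y.

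| D (days) | ρ₁ | × binomial | f | c (k = 0.063, y = 540) |
|---|---|---|---|---|
| 10 | 0.55 | 2.21 | 1.99 | 9.9 |
| 15 | 0.65 | 2.74 | 2.46 | 11.8 |
| 20 | 0.72 | 3.34 | 3.01 | 14.0 |

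Power at nine per arm:

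| D (days) | k = 0.063, y = 540 | k = 0.063, y = 480 | k = 0.20, y = 540 |
|---|---|---|---|
| 10 | 76% | 71% | 51% |
| 15 | 67% | 63% | 47% |
| 20 | 59% | 55% | 42% |

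A day-by-day simulation gave f = 1.96–2.92 with fixed lengths and 2.4–3.8 with geometric lengths. At k = 0.063 and y = 540, power falls below 80% once f exceeds 1.77.

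**Reading B: new episodes are counted.** A long episode counts once. In simulation at 0.1 per child-week with 10–20 day episodes the factor was 0.57–0.79, so duration does not inflate the variance. The rate must then be an onset rate. A 10% weekly prevalence gives 7×(−ln 0.9)/L = 0.046 (D = 10, L = 16) to 0.028 (D = 20, L = 26) episodes per child-week. With f = 1, k = 0.063 and y = 540, c = 10.6–16.1 and power is 72%–53%. The article's three episodes a year (0.057 per week) gives 81% at y = 540, 76% at 480 and 71% at 420.

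**Longer follow-up, Reading A.** 24 weeks with 35 retained children gives y = 840, with f = 2.04/2.56/3.17. Power is 89%/83%/75% at k = 0.063 and 59%/55%/50% at k = 0.20.

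**The case against.** The strongest reply is that the calculation names incidence density, on which long episodes add no variance. That stands, and it rules out the factor of 2–3 for new-episode counts. It does not rescue the input: 0.1 is then a prevalence used as an onset rate, and the matching onset rates give 72%–53%. Differences in risk between children could inflate the variance on this reading too, but the article gives no figure for them.

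Second, 12 weeks is a minimum. The diary runs 12 months and the intervention-only phase lasts 8 months. This also stands: at the printed k, 24 weeks largely restores the power. The article nevertheless ties its 80% to 12 weeks and does not say how many diary weeks will be counted.

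Third, Table 1 reports under-four prevalence of 45.9% and 45.7%, not 10%. If those are 7-day figures and the 25% reduction holds, f is only about 1.1–1.7. Power at y = 540 is then about 100% at k = 0.063 and 73%–76% at k = 0.20. The size of the problem therefore depends on the planned 10%.

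Fourth, the 10–20 days is not expressly per episode, although the primary outcome defines duration that way. Three episodes a year of that length imply roughly 12%–19% weekly prevalence, so the article's inputs do not fit one another.

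Finally, k is the larger error and does not depend on the reading. That is correct; this point adds to it.

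**Conclusion.** The point holds in a conditional form. The sample size uses one number as both prevalence and incidence rate and has no term for repeated weeks in a child. At 12 weeks, with 10% taken as a one-week prevalence and fixed episodes of 10–20 days, nine quartiers per arm give about 76%–59% (ill weeks) or 72%–53% (new episodes) at the printed k and y = 540. Only the three-episodes-a-year input reaches 80% there (81%), and it drops to 76% at the 480 child-weeks that 40 children supply. With k = 0.20, the ill-week figures are 51%–42%, against 63% with independent weeks.

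A reader might infer that episode length by itself makes the variance two to three times too small and the trial underpowered. The article does not support that: the factor applies only to ill/not-ill scoring, the follow-up may be longer than 12 weeks, and the baseline prevalence is far above 10%. What is shown is that the stated 80% is unsupported, not that the trial must miss it.

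**What to change.** Make these changes under Sample size calculation, together with the correction of k:

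1. State whether a child-week event is a new episode or an ill week.
2. Use the matching rate. For new episodes, use an onset rate and reconcile it with the three episodes a year in the Discussion.
3. For ill weeks, replace (λ0+λ1)/y by f(λ0+λ1)/y with a stated f: about 2–3 at 12 weeks, or an estimate from early diary weeks made blind to arm.
4. State how many diary weeks are counted, and the child-weeks per quartier that follow from 40 sampled children and 12.5% loss.
5. Restate the power that nine quartiers per arm deliver.

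This takes a few lines of recalculation and needs no further enrolment. The downside is that the stated power becomes less favourable.

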**Discussion:**

Material subsidies will be provided only to the households who complete pit digging plus superstructure and roof construction, regardless of their income level. This study employs a Sanitation Calendar so that the mother of each household can record the diarrheal episodes of her under-four child on a daily basis. The diary enables examination of the effect of the sanitation intervention on diarrhea duration and also resolves the limitation of the small number of clusters in the trial.

In addition, the project will be monitored through the ‘Sanitation Map’, on which all households in the study area, including both the control and intervention arms, are registered. To avoid information bias or courtesy bias, photos will be taken of the latrine during the household visit, and a supervisor will determine well-equipped latrine uptake based on the photos. This reduces the possibility of recall bias and under- or over-estimation of diarrhea, which was the main limitation of previous studies.

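### The sample size rests on a miscalculated between-cluster coefficient of variation (0.063 instead of 0.200), and k = 0.3 does not give seven clusters, so nine quartiers per arm fall short of 80% power

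*Protocol article*

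**What the plan says.** All figures are in the protocol article, section Sample size calculation, unless stated otherwise.

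- The expected variance of the observed cluster rates is written as λ·Av(1/y) plus σ²c, and σ²c is set equal to k²λ². The legend ends "and k is the coefficient of variation of those rates".
- The inputs come from a preliminary survey of 20 quartiers with an overall rate of 0.1 per child-week. "The empirical standard deviation of the observed diarrhea rates was s = 0.051216", and the mean reciprocal child-weeks is 0.022222. The section then takes k = √(0.000401/0.1) = 0.063.
- With k = 0.063313, y = 540 child-weeks per quartier and rates of 0.1 and 0.075, it reports c = 6.14 per arm. Against 4.07 quartiers without clustering it states that "the expected design effect for this trial would be 6.14/4.07 = 1.51".
- A second scenario follows: "Assuming a coefficient of variation of 0.3 with 80% study power and 7.5% diarrheal prevalence in the intervention resulted in seven clusters" per arm. This is raised to nine per arm with 360 households per arm, at least 12 weeks of follow-up and 12.5% loss.
- The Abstract says that the diary "resolves the limitation of the small number of clusters in the trial". The main Discussion repeats that it "resolves the limitations associated with the small number of clusters in the trial".

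**The concern.** The computed k does not match the definition of k given a few lines earlier, and the two cluster counts do not follow from the formula they are attributed to. A count of 6.14 at k = 0.063 and one of seven at k = 0.3 cannot both come from one formula, because k² differs by a factor of more than 20.

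If the figures are wrong, the move from seven to nine quartiers is not a safety margin but a shortfall, and the 80% power claim has no basis. That affects how any result would be interpreted. The trial is presented as an answer to earlier sanitation trials that found no effect, so readers need to know which reduction it could reliably detect.

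**Working it through.** **Formulas, as in the plan.** σ²c = s² − λ·Av(1/y) and k = σc/λ. Then c = 1 + (1.96 + 0.84)²·[(λ0 + λ1)/y + k²(λ0² + λ1²)]/(λ0 − λ1)². With λ0 = 0.1 and λ1 = 0.075 this is c = 1 + 7.84·[0.175/y + 0.015625k²]/0.000625. The 1.96 implies a two-sided 5% level. The text prints z_β as 1.96 for 80% power, but the formula uses 0.84, so I take that as a misprint.

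**Step 1: k.** σ²c = 0.051216² − 0.1 × 0.022222 = 0.002623 − 0.002222 = 0.000401, which reproduces the plan. √(0.000401/0.1) = 0.0633 also reproduces the printed value. By the plan's definition k = √0.000401/0.1 = 0.0200/0.1 = 0.200. So k is understated about 3.2-fold and k² tenfold.

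**Step 2: the printed 6.14.** With k = 0.063313 and y = 540: 0.175/540 = 0.0003241 and 0.015625 × 0.004009 = 0.0000626. The sum divided by 0.000625 is 0.6187; times 7.84 is 4.85; plus 1 is 5.85. The value 6.14 appears only at y = 504, whereas 4.07 = 2195.2/540 uses 540. The ratio 1.51 therefore mixes two denominators. It also keeps the +1 in the numerator only. Without the +1, and at y = 540 throughout, the plan's k gives 4.85/4.07 = 1.19.

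**Step 3: corrected k.** At y = 540: 0.0003241 + 0.0006263 = 0.0009503; /0.000625 = 1.5205; × 7.84 = 11.92; + 1 = 12.9. The design effect without the +1 is 11.92/4.07 = 2.9.

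**Step 4: k = 0.3.** At y = 540: 0.0003241 + 0.0014063 = 0.0017303; /0.000625 = 2.7685; × 7.84 = 21.7; + 1 = 22.7. With unlimited child-weeks: 7.84 × 2.25 + 1 = 18.6. A one-sided test (14.9 with unlimited child-weeks) does not give seven either. Seven is what the erroneous k yields: 6.14 rounded up, or 7.01 at y = 420. Seven per arm at k = 0.3 have 30–31% power for y = 420–540.

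**Step 5: power of nine per arm.** Power = Φ(√(8 × 0.000625/[0.175/y + 0.015625k²]) − 1.96). For example, at k = 0.200 and y = 540: √(0.005/0.0009503) − 1.96 = 0.334, so 63%. A noncentral t with 16 df agrees within 0.5 points. Households per quartier are 360/9 = 40.

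| y per quartier | Source | c, k = 0.200 | Power, 9 per arm | c, k = 0.3 | Power, 9 per arm |
|---|---|---|---|---|---|
| 420 | 40 × 12 × 0.875 | 14.1 (15) | 59% | 23.9 (24) | 38% |
| 480 | 40 × 12 | 13.4 (14) | 61% | 23.2 (24) | 39% |
| 540 | plan | 12.9 (13) | 63% | 22.7 (23) | 40% |
| 1820 | 40 × 52 × 0.875, assumed | 10.1 (11) | 75% | 19.8 (20) | 45% |
| 2080 | 40 × 52, assumed | 9.9 (10) | 76% | 19.7 (20) | 45% |
| unlimited | limit | 8.9 (9) | 81% | 18.6 (19) | 47% |

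With the erroneous k = 0.063, nine per arm would appear to have 90–95% power at y = 420–540.

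**Step 6: detectable reduction.** Solving c = 9 for λ1 at 80% power and y = 540 to 420 gives a reduction of 30–31% at k = 0.200 and 39–40% at k = 0.3.

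**The case against.** The errors in k, in 6.14 and in the seven clusters cannot be defended from the text. The serious objections concern how far the consequences reach.

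- **Flat power of about 60%.** A reader might infer that the trial simply has about 60% power. The documents do not support that as a single figure. It is tied to 420–540 child-weeks per quartier. The section on the Sanitation Calendar plans 12 months of daily recording, which would bring power at k = 0.200 to about 75%. Against this, Study design gives the control arm the intervention after an 8-month first phase, so the randomised contrast may be shorter than 12 months.
- **The 8640 child-weeks.** The plan states this number per quartier. Taken literally it gives 79% power at k = 0.200, but 720 × 12 = 8640 is the whole-trial total.
- **The diary statement as plainly false.** A reader might infer this from k = 0.3. At k = 0.200, however, more child-weeks help substantially: the requirement falls from 12.9 at y = 540 to 9.9 at y = 2080, and nine per arm approach 81% in the limit. The wording is overstated rather than without foundation.
- **A design effect of 3.2.** A reader might replace 1.51 by 12.9/4.07. That repeats the fault of counting the +1 on one side only; the consistent value is 2.9.
- **Imprecision and other assumptions.** k comes from 20 quartiers averaging about 45 child-weeks. A chi-square 95% interval on s² (normality assumed) puts k anywhere from 0 to about 0.58. Table 1 shows under-four prevalence near 46%; if that were the weekly rate (an assumption, as prevalence is not incidence), power at y = 540 would be about 76% for k = 0.200 and 45% for k = 0.3. Quartiers were also allocated in groups with eight possible allocations, so the formula's independence of clusters is only approximate.

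These points stand as conditions on the restated power. None restores the printed k, 6.14, 1.51 or seven, and none brings k = 0.3 near 80%.

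**Conclusion.** The point holds. By the plan's own definition and inputs k is 0.200, and the formula then needs 13 quartiers per arm at 540 child-weeks, or 15 at 420. The seven clusters claimed for k = 0.3 are wrong at any follow-up length. Nine per arm do not deliver the stated 80% power for a 25% reduction at the planned child-weeks.

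The size of the shortfall depends on k and y. At k = 0.200 it is moderate to large, and the 12-month figure assumes that all 40 diaries per quartier are usable and that the contrast lasts that long. At k = 0.3, the value from which the plan takes its seven clusters, power stays below 50% however long the diary runs. All figures assume a control rate of 0.1 per child-week, a two-sided 5% level and independent quartiers. It would go too far to infer from this how a null result will be read; the documents do not say.

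**What to change.** Text and figures only, in Sample size calculation, the Abstract and the Discussion:

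1. Correct k to 0.200, and say that it is an imprecise estimate from 20 quartiers.
2. Replace 6.14 by 12.9 (13 per arm) at y = 540, and give 14.1 (15 per arm) at y = 420 after 12.5% loss. Replace the design effect of 1.51 by about 2.9, computed without the +1.
3. Replace the seven clusters at k = 0.3 by 22.7 (23 per arm) at y = 540.
4. State the power and detectable reduction of nine per arm for both values of k, each tied to a named y and period of observation, using the values in the working.
5. Replace both statements about the calendar with wording that more child-weeks reduce only within-cluster error and leave between-cluster variance unchanged.
6. Correct the printed z_β in the same edit.

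No clusters or households need to be added. The cost is a less favourable power statement.
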